
#### Qualitative interviews

At the 6-month follow-up (T2), child-parent dyads in the intervention group and HCPs will be interviewed to assess their experience of participating in the trial, the acceptability of the intervention and their overall experience. All participants who drop out will be approached for an interview. The interviews will explore: (1) the willingness of participants to be randomised, (2) whether children enjoyed the STAK-D programme or not, and why, including how it made children feel, (3) children’s satisfaction with the wrist-worn activity monitor (PolarActive), (4) barriers to participation in the STAK-D programme, including reasons for nonadherence, (5) acceptability of the research processes including reasons for attrition and missing data, (6) whether parents and children thought that the intervention was beneficial, useful and easy to incorporate into daily routine, (7) children’s and parents’ perceived reasons for, and response to, any changes in outcomes, (8) willingness of HCPs to be involved in recruitment, (9) willingness of HCPs to receive and reply to emails from STAK-D programme users (via the ‘Ask the Expert’ section on the website), (10) suitability of the clinic setting for recruitment and (11) whether the inclusion criteria were deemed appropriate by patients, parents and HCPs.

#### Health care costs

Estimated costs relevant to recruitment, screening, intervention implementation and follow-up will be calculated. We will also estimate retrospectively the health care resource use and cost them at national rates.

### Secondary outcome measures

The following standardised measures have adequate psychometric properties and have been used in other studies with children of the same age range who have T1DM [22] or other long-term conditions [21]. Our previous research [22] and significant patient and public involvement activities have indicated that the assessments may take approximately 45–60 min to complete. The outcomes measured at T0, T1 and T2 will be:

#### Child measures

I.Self-reported physical activitySelf-reported frequency of different types of physical and sedentary activities will be assessed with a 55-item physical activity questionnaire (PAQ) [46] adapted from the full 80-item PAQ [47]. The questionnaire refers to the previous 24 h and children are asked to rate a range of activities, on a three-point scale (none, a little, a lot) at three time points (yesterday afternoon, last night, this morning). Higher scores indicate greater frequency of engagement in physical activity. The authors of the PAQ reported good agreement between questionnaire responses for PAQ and observed activities [47]. Furthermore, combining interview technique with probing activity in the recent past is considered most likely to generate results that correlate with objective measures of activity [48]. The 55-item PAQ has been found to discriminate physical activity levels in children attending paediatric outpatient clinics [46]II.Self-efficacy for physical activityChildren’s self-efficacy for physical activity will be measured using the Children’s Self-Perceptions of Adequacy in, and Predilection for, Physical Activity scale (CSAPPA) [49]. CSAPPA is a 20-item scale to measure the self-perception of confidence in, preference for, and enjoyment of physical activity. CSAPPA is composed of three subscales: (1) perceived adequacy (perceived ability to achieve some level of successful with respect to being physically active), (2) predilection toward physical activity (preference for being active over being sedentary when given the choice) and (3) enjoyment of physical education class. The scale employs a structured alternative choice format. Children are asked to choose the option that best describes them from pairs of statements about other children such as, ‘Some kids can’t wait to play active games after school’ and ‘Other kids would rather do something else’ by indicating whether the sentence was either ‘sort of true for me’ or ‘really true for me’. Higher scores for subscales indicate greater perceived adequacy, predilection for, and enjoyment of physical activity. The scale was designed by Hay (1992) [49] for 9–16 year-olds and has demonstrated high test-retest reliability and strong predictive and construct validityIII.Fear of hypoglycaemiaChildren’s fear of hypoglycaemia will be assessed using the Child Hypoglycemia Fear Survey (CHFS) [50]. CHFS is comprised of a 10-item behaviour (B) subscale and a 15-item worry (W) subscale. HFS-B items describe behaviours performed in order to avoid hypoglycaemic episodes and/or their negative consequences (e.g. by limiting exercise or physical activity). HFS-W items ask about specific concerns about hypoglycaemic episodes (e.g. episodes occurring during sleep, or having an accident). Higher scores indicate greater fear of hypoglycaemia. Previous research has indicated that the children’s HFS is a valid and reliable measure of youth fear of hypoglycaemia and that it significantly correlated with other measures of anxiety [50]IV.Health-related quality of lifeChild Health Utility 9D (CHU9D) [51] is a health-related quality of life measure for children aged 7–17 years, which allows the calculation of quality-adjusted life years (QALYs) for use in cost-utility analysis. It consists of nine items (worry, sadness, pain, tiredness, annoyance, school, sleep, daily routine and activities) each represented by a single question with five response options (scored 1–5). Higher scores indicate better health-related quality of life. The recall period is today/last night. The CHU9D has demonstrated validity in paediatric clinical populations [52]V.Communication questionnaireA short questionnaire developed specifically for this study will be used to explore children’s perceptions of the communication around physical activity they have with their diabetes team. It contains two items and assesses children’s perceptions of (1) frequency of physical activity discussion (e.g. ‘In the last 6 months, have you spoken to one of your diabetes doctors or nurses about physical activity, exercise or sport?’ and, ‘If yes, how many times (1–5+)?’) and (2) difficulty of physical activity discussions (e.g. ‘talking to your diabetes doctors and nurses about physical activity, exercise or sport is…..?’ (5-point scale; really hard to really easy))VI.Objective physical activityPhysical activity will be measured objectively using a PolarActive wrist-worn activity watch (Polar Electro Inc., Lake Success, NY, USA) at T0, T1 and T2 in intervention and control group children. Wrist-worn activity monitors have demonstrated acceptability and feasibility among children with T1DM in previous research [22]. The PolarActive device has shown to be preferred by children aged 7–10 years compared with other devices, and is associated with the highest level of compliance [53]. Children will be given the PolarActive watch for 7 days at each time point, and start date (day of the week) will vary according to recruitment date; we will monitor patterns of physical activity over the data collection period. Day 1 will be considered as a familiarisation day to minimise potential reactivity and data will be analysed if activity watches are worn for at least 600 min on at least 3 days. Physical activity will be measured as step counts and average minutes in moderate-to-vigorous physical activity per dayVII.Clinical outcome measuresThese measures are routinely collected by the diabetes health care team and, with consent, will be taken from the child’s clinic notes. The measurement that coincides most accurately with the data collection period (T0, T1 and T2) will be taken.
*Glycosylated haemoglobin (HbA1c)* – as an indication of diabetes control
*Insulin dosage –* to explore changes as a further indicator of diabetes control. Insulin dosage is downloaded at standard clinic appointments using diabetes management software (e.g. Diasend/Carelink Diabetes Management); we will assess the feasibility of collecting this information from routine clinic notes. Total daily insulin dose will be recorded where possible, and we will examine the practicality of collecting this data, and subdividing it into basal and bolus doses
*Body composition* – Body Mass Index (BMI) will be calculated from height (cm) and weight (kg)

The primary outcome to be used in a future large-scale RCT is projected to be a change in self-efficacy for physical activity as measured by the CSAPPA scale. However, the choice of additional primary outcome measures will be finalised after taking into account the results of the feasibility study.

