#### Outcome measures

Outcome measures will be completed at baseline (T0), 8 weeks (T1) and 6 months (T2).

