#### Primary outcome measures

The primary outcome measures for the feasibility study are as follows:Recruitment rateAn estimate of the number of eligible patients and likely uptake rate will be assessed. The response rate for mailed invitation will be compared to clinic (face-to-face) recruitment rates. Refusal rate and reasons for nonparticipation will be assessed. This will enable a prediction of recruitment rate, number of sites and length of time needed to recruit the required number of patients for a future trial. A recruitment rate of between 25 and 40% would be considered reasonable based on our previous research [22] and similar studies [44, 45]Adherence ratePattern of intervention use will be monitored to assess fidelity of intervention delivery. We will explore users’ activity by website and page visits, more or less commonly used elements, and engagement with goal-setting and activity tracking. We will assess user satisfaction with STAK-D (e.g. navigation, ease of use, technical issues) at 6 months. Acceptable compliance will be defined as the child using the online resources and tracking their daily activity (using the PolarActive watch). Noncompliance will be defined as the child’s failure to access the STAK-D website and track their physical activity over the intervention periodRetention rateRetention will be defined as the number of participants completing the STAK-D programme including all scheduled follow-up data collection (T0, T1 and T2) compared to the number started. A retention rate of at least 70% at each time point would be considered feasible based on our previous research [22] and similar studies [44, 45]Data completion rateCompletion of outcome measures will be recorded at T0, T1 and T2 (complete and partial or noncompletion with reasons, including time to complete). Measures will be determined acceptable to parents and children (in terms of literacy, cognitive ability and capacity to understand) if more than 70% are fully completed (indicating quality data), and reported participant burden is minimal.The feasibility of gathering routinely collected clinic data from patients’ electronic diabetes record (height, weight, HbA1c level and insulin dosage) at T0, T1 and T2 will be assessed. This will allow us to ascertain the proportion of our sample with complete clinical records, and whether records will be accessible to our researchers at specified data collection time points. Feasibility of collecting observational data in this way will be determined if more than 85% of the sample have complete clinical records availableAdverse eventsAny adverse events experienced as a result of participation in the intervention will be recorded and evaluated. Adverse events are defined as any serious negative outcome resulting from the physical activity undertaken as part of the STAK-D programme. Severe hypoglycaemia, i.e., a blood glucose level below 4 mmol/l requiring the help of another person to treat it, will be considered an adverse event in either group. Data from meter and pump downloads combined (and meter downloads alone for those patients not on insulin pump therapy) will be used for identification of hypoglycaemic episodes, as per usual care at our participating sites. To determine the likelihood of adverse events being associated with the physical activity undertaken as part of the STAK-D programme, we will record whether the frequency and/or severity of hypoglycaemic episodes increased during the intervention period. The occurrence of adverse events related to the intervention will be assessed and compared to the control group (see ‘Harms’ section for potential adverse events).

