### Recruitment

Potential participants will be recruited from paediatric diabetes clinics at the two hospital sites. They will be identified and approached by a member of the clinical team via a postal invitation pack (including letter, Participant Information Sheets (PIS) and Expression of Interest (EOI) Form). Children will receive a child-friendly version of the PIS. If the child and parent are willing to hear more about the study, they will return the EOI to the research team, and will be introduced to the researcher at their next clinic appointment for a detailed discussion about the study. At this prestudy screening meeting, consent will be received, baseline data collected and randomisation performed. Participants will be randomised after baseline data has been collected. The researcher and/or principal investigator will receive written informed consent from the parent and written informed assent from the child prior to the participant undergoing any research procedures. There must be mutual agreement between the child and parent for the child to participate.

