### Data collection, management and analysis

#### Data collection methods

Participants will have six visits for data collection. Visits will take place at either the child’s usual paediatric diabetes clinic or another mutually convenient location (e.g. the participants’ home) depending on parent preference, and preferred locations for data collection will be recorded. Children and parents will complete the assessments at visits 1 (baseline/T0), 3 (T2) and 5 (T3). Children will be assessed for self-reported physical activity (PAQ), self-efficacy for physical activity (CSAPPA scale), fear of hypoglycaemia (CHFS), health-related quality of life (CHU9D), clinician-patient communication and objective physical activity (PolarActive). As close to visits 1, 3 and 5 as possible, the researcher will ask the clinician for clinical data from the participants’ clinical records (height, weight, HbA1c level and insulin dosage). Parents will be assessed for demographics, fear of hypoglycaemia (PHFS), child’s quality of life (CHQ-PF28) and additional self-reported items. One week after visits 1, 3 and 5 (at visits 2, 4 and 6), data from the activity watch will be downloaded. Health care professionals drawn from the paediatric diabetes teams at the study sites will be asked to complete a clinician-patient communication questionnaire at T0, T1 and T2.

At visit six, all child-parent dyads in the intervention group will be invited to participate in single exploratory interview as part of the process evaluation. All participant dyads who have dropped out of the study will be invited to interview (at the point when they leave the study). For practical reasons child and parent will be interviewed together with questions/topics directed to each as appropriate. Interviews will be undertaken face-to-face at a time and venue convenient to the family.

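### Clinic records are chosen as nearest to each time point with no window, so the 85% records criterion, if judged on them, is blind to timing and T1 values may be weeks late or the baseline value

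*Protocol article*

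**What the plan says.** The Child measures section, under clinical outcome measures, takes HbA1c, insulin dosage, height and weight from the child's routine clinic notes. The study makes no measurement of its own for these items. The selection rule is "The measurement that coincides most accurately with the data collection period (T0, T1 and T2) will be taken". The Data collection methods section adds a second timing statement: "As close to visits 1, 3 and 5 as possible, the researcher will ask the clinician for clinical data from the participants’ clinical records".

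The time points are baseline (T0), 8 weeks (T1) and 6 months (T2). Under Recruitment, families who express interest "will be introduced to the researcher at their next clinic appointment for a detailed discussion about the study", and baseline data are collected at that meeting. Under Data collection methods, study visits may instead be held at home or another agreed place.

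The pass mark is under Primary outcome measures, data completion rate. Collecting the four items from records counts as feasible if more than 85% of the sample have complete records. The same paragraph gives two purposes: to learn what proportion of records are complete, and "whether records will be accessible to our researchers at specified data collection time points".

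**The concern.** A nearest-record rule with no limit always returns a value. A child with one clinic entry holding all four items has a nearest measurement for T0, T1 and T2 alike, and nothing stops that entry from serving all three. A count of complete records built this way answers the first stated purpose of the criterion but not the second.

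Two things are at stake. A pass could lead the team to rely on routine records for an 8-week outcome in the definitive trial when those records hold nothing near 8 weeks. Also, the T1 changes in HbA1c, BMI and insulin dose could be mistimed or zero by construction. The secondary objective uses the variability of outcome measures, these included, to plan the next trial.

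**Working it through.** **Inputs.** T0, T1 and T2 are weeks 0, 8 and 26 (6 months taken as 26 weeks). T0 falls at a clinic appointment (Recruitment). The target is 50 dyads; 70% retention leaves 35. The interval between clinic appointments, L weeks, is not in the document and is varied from 6 to 26.

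**The threshold.** The 85% is a chosen mark with no calculation behind it to reproduce. More than 85% of 50 is more than 42.5, so at least 43 children. More than 85% of 35 is more than 29.75, so at least 30.

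**Regular appointments at weeks 0, L, 2L and so on.** The baseline record is 8 weeks from T1. For L of 8 or more, the next record is L − 8 weeks from T1. The later record is nearer when L − 8 < 8, that is, when L < 16.

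| L (weeks) | Record nearest to week 8 | Offset at T1 (weeks) | Offset at T2 (weeks) |
|---|---|---|---|
| 8 | week 8 | 0 | −2 |
| 10 | week 10 | +2 | +4 |
| 12 | week 12 | +4 | −2 |
| 13 | week 13 | +5 | 0 |
| 14 | week 14 | +6 | +2 |
| 16 | tie: week 0 or 16 | ±8 | +6 |
| 20 | week 0 (baseline) | −8 | −6 |
| 26 | week 0 (baseline) | −8 | 0 |

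If the data request at visit 3 can return only records that already exist, any L above 8 weeks gives the baseline record. The text does not settle whether later records may be used.

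**Irregular appointments.** With intervals simulated as normal with mean 12 or 13 weeks and an assumed SD of 3 weeks:
- The baseline record is reused as T1 in 9% (L = 12) and 16% (L = 13) of children.
- The T1 value is at least 4 weeks late in 41% and 47%.
- The nearest record lies within ±4 weeks of T1 in 50% and 37%, within ±4 weeks of T2 in 72% and 69%, and within ±4 weeks of both in 33% and 25%.
- Within ±2 weeks, the T1 figures are 23% and 15%, and the T2 figure is 38% for both.

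**Effect on T1 change.** Suppose a fraction f reuses baseline, unrelated to the true change. The mean change, and any between-arm difference in it, is then multiplied by 1 − f. If the mean change is small, the SD is multiplied by √(1 − f). For f = 0.091 the factors are 0.909 and 0.953; for f = 0.16 they are 0.84 and 0.917. The mean is therefore 9–16% too small and the SD about 5–8% too small, before any effect of late values.

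**Effect on the criterion.** Let p be a child's probability of counting as complete and X the number complete, binomial (50, p). The chance of passing is P(X ≥ 43):

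| p | Chance of passing |
|---|---|
| 0.95 | 0.997 |
| 0.90 | 0.88 |
| 0.85 | 0.52 |
| 0.80 | 0.19 |
| 0.70 | 0.007 |
| 0.60 | below 0.001 |

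Under the nearest-record rule, p depends only on whether the four items are recorded at all. With a ±4-week window and the irregular schedule above, timing alone caps p at about 0.37–0.50 for T1 and about 0.7 for T2, and the criterion would very probably fail. Under that assumed schedule, the same clinic data could give opposite conclusions depending on how the sentence is read.

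**The case against.** The strongest reply is that windows and tie-breaking belong in the SAP, which the protocol promises before analysis, and that an article condenses a fuller document. This stands for the width of a window. It does not dispose of the point, because the article itself states the selection rule, the numerical pass mark and the purpose, and as stated the first two do not serve the third. The article does set a validity minimum for the activity watch (600 minutes on at least 3 days), so this level of detail was not left out on principle.

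Second, the 85% criterion does not cite the selection rule. Its paragraph speaks of records at the three time points, and a sensible reader might not count a child with no record near week 8 as complete. This stands, and it makes the point conditional. But nothing says how far is too far, so two analysts could reach opposite results.

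Third, using a pre-randomisation value as T1 strains the idea of coinciding with T1. That is fair as to intent, but nothing bars it.

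Fourth, any window is arbitrary, and reporting days from target would inform the reader without one. Reporting dates is part of the remedy, but a pass/fail criterion still needs a definition of what counts.

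**Conclusion.** The point holds in a limited form. The selection rule has no distance limit, no direction and no bar on reuse. If the 85% criterion is judged on records chosen this way, it cannot detect mistimed records, although accessibility at the time points is one of its stated purposes. T1 values are 4–6 weeks late at an assumed regular interval of 12–14 weeks, and are the baseline value above 16 weeks. Both results assume that T0 falls at a clinic appointment and that records on either side of T1 may be used.

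Three stronger readings are tempting but not supported:
- **That the criterion is nearly impossible to fail.** It needs four items, and the protocol itself doubts insulin dose, which is to be recorded only where possible. At a per-child completeness of 0.80, it passes with probability only 0.19.
- **That T1 change will be zero for most children.** Under nearest-record selection this needs intervals above about 16 weeks, and the document gives no interval. At 12–13 weeks with an SD of 3 it affects 9–16%.
- **That the main design input for the next trial is compromised.** HbA1c, BMI and insulin dose are secondary here. The projected primary outcome, the CSAPPA self-efficacy scale, is collected at study visits and is untouched.

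**What to change.** Replace the nearest-record sentence with a rule on these lines:
- T0 is the last value on or before randomisation.
- T1 and T2 are the closest post-randomisation values within a prespecified window, for example ±4 weeks (weeks 4–12 and 22–30, which do not overlap). The width is the team's choice.
- Each record is used once, and a value outside the window is missing for that time point.
- The 85% criterion is judged separately at each time point, on in-window records of all four items.
- The date of each measurement is recorded and the distribution of days from target is reported.

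This changes wording only and needs no extra visit or measurement. The cost is a less favourable completeness rate, especially at T1, and the window chosen may largely decide the result. It should therefore be fixed before the record dates are seen. Reporting days from target lets readers judge other widths.
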